## Abstract

**Background:**

Sickle cell anaemia (SCA) is an inherited disorder of haemoglobin. Patients experience long**-**term health care problems, affecting quality of life (QOL) including frequent acute pain, which is difficult to document in trials except as hospital admissions. Pilot data suggests that overnight respiratory support, either supplementary oxygen or auto**-**adjusting continuous positive airways pressure (APAP), is safe and may have clinical benefit. This pilot trial aims to determine which intervention is more acceptable to participants and whether there are other advantages of one over the other, e.g. in respiratory function or haematological parameters, before conducting the Phase 2 trial of overnight respiratory support funded by the National Institutes of Health Research.

**Methods/Design:**

This is a pilot cross**-**over interventional trial with the order of interventions decided by simple randomization. Ten adults (age over 18 years) and 10 children (aged between 8 and 18 years) with homozygous sickle cell disease (haemoglobin SS, HbSS), recruited regardless of symptoms of sleep**-**disordered breathing, will undergo overnight pulse oximetry and will have two interventions, overnight oxygen and APAP, for a week each in randomised order with a washout week between interventions. Participants will complete online diaries via an iPad throughout the 29 days of the study and will complete QOL questionnaires and have measurement of haematology, biochemistry, spirometry and lung volumes (adults only) at 3 time points, at baseline and after each intervention, as well as in-depth semi-structured qualitative interviews after each intervention, carried out by an experienced psychologist. Both qualitative and statistical methods will be used to analyze the data. The primary outcome is qualitative data looking at participant experience from the transcribed interviews after each intervention. The participant’s view on feasibility, acceptability and preference will specifically be explored. The QOL, laboratory and lung function data will be compared with baseline for each arm.

**Discussion:**

Patient and public involvement is an integral part of this trial and the key outcome is the qualitative result, which is dependent on obtaining good quality data to advise on participant feasibility, acceptability and preference. This is being addressed by using a standard interview. The development of a pain endpoint is another important outcome and collecting daily measurements is likely to be challenging. Research results will be used to inform design of the Phase 2 trial.

**Trial registration:**

ISRCTN46078697 18 July 2014

**Electronic supplementary material:**

The online version of this article (doi:10.1186/s13063-015-0883-y) contains supplementary material, which is available to authorized users.

## Background

Sickle Cell Anaemia (SCA) is a recessively inherited disorder of haemoglobin, the protein which carries oxygen inside red blood cells. SCA affects an estimated 15,000 people [1] in the UK and patients experience long**-**term health care problems, including pain and neurocognitive problems, which affect quality of life. Emergency presentations are typically due to acute sickle cell pain [2, 3] and account for over 6000 emergency admissions and over 25,000 bed days per year [4]. Mortality in children in England has improved over recent years with around 99 % now surviving to 18 years [5]. Life expectancy is, however, shortened to 40–50 years [6, 7] and quality of life is compromised by chronic complications [8–16].

The prevalences of *intermittent* nocturnal haemoglobin oxygen desaturation, secondary to sleep**-**disordered breathing, and *sustained* daytime and nocturnal haemoglobin oxygen desaturation, are high in patients with SCA [17–22]. There is an association between low oxygen saturation (SpO_2_) and SCA complications, including stroke [12, 23], enuresis [14] and priapism [15] as well as painful crisis [3], although the latter is controversial [18], perhaps related to differences in documentation of painful crisis. Cognitive function, including impaired attention, is a particular problem in SCA [24–29], and may be linked to sleep**-**disordered breathing and oxygen desaturation [25–29], as it is in the general population.

Treatment options for sleep**-**disordered breathing and nocturnal hypoxia include continuous overnight oxygen via a concentrator and continuous positive airways pressure (CPAP) but there are few data on their use in SCA. These two interventions commonly used to reduce overnight hypoxic exposure have different modes of action and there are some preliminary data available for each:Positive Airways Pressure. CPAP therapy reduces sleepiness in adults and children with obstructive sleep**-**disordered breathing in the general population and may improve cognition and intermediate vascular endpoints [30–33] but adherence is an issue [31]. Auto**-**adjustable CPAP (APAP) is more comfortable as the pressure support is only triggered when the obstruction occurs [34].
*Positive Airways Pressure in SCA* Positive airways pressure has been used short**-**term in SCA in acute chest crisis [35] and to prevent peri**-**operative complications [36]. In unselected children with SCA in our 6**-**week proof**-**of**-**concept randomised controlled trial (RCT), overnight respiratory support with APAP was safe and feasible, with excellent adherence in all 12 participants in the treatment arm and no suppression of erythropoiesis [37]. Improvement in cancellation (Wechsler Intelligence Scale for Children (WISC**-**
^IV^UK)), a measure of attention as well as processing speed, was seen in those on APAP compared with those not treated [37]. Pain frequency, defined as the number of days that pain was experienced in a 2**-**week period, improved in the treatment arm (*p* = 0.07) but this did not reach statistical significance, perhaps related to reduced statistical power due to reluctance to complete paper pain diaries (full data was only available for 8 of the 12 participants in each arm) [37]. As pain is the cardinal symptom in sickle cell disease, and is, therefore, an important endpoint in clinical trials, ensuring that all participants complete any diaries is important. With smartphone technology [38], daily pain intensity and site may be explored in addition to frequency [39], number of days in hospital [3] or number of admissions [20].Overnight oxygen is well**-**established for the treatment of hypoxia secondary to lung diseases, such as chronic obstructive airways disease in adults or bronchopulmonary dysplasia. Uncontrolled hypercapnia is a risk in settings where respiratory failure may occur [40].
*Oxygen supplementation in SCA* There are few data on the safety of oxygen administration in people with SCA and most data is available over short periods of time, typically in the management of acute crisis. The two main concerns in using overnight oxygen in SCA are the suppression of erythropoiesis and rebound pain, which has been documented with the administration of high flow rates of oxygen throughout 24**-**hour periods for several days [41]. However, reticulocytosis was documented in a child whose abdominal pain was relieved by 18 days placement within an oxygen tent [42]. In addition, erythropoietin levels did not fall in non**-**hypoxic adults randomised to receive oxygen during a painful crisis [43]. Although the duration of painful crisis was not reduced by the administration of oxygen in this study [43] or a paediatric trial designed to administer 50 % oxygen [44, 45], there was no evidence of rebound pain.One report audited the use of long**-**term oxygen supplementation in SCA. Ip et al [46] described 6 adults with SCA (age range 20–45 years; 4 women), who had been commenced on oxygen therapy (1**–**2 l/minute) in the previous 2 years because of nocturnal hypoxia, defined as oxygen saturations < 90 % for > 30 % of the night. A detailed case notes review showed a mean increase in haemoglobin and reticulocyte count, with no change in erythropoietin and painful episodes.

There is a possibility that overnight respiratory support improves daytime lung function [47, 48] and oxygen saturation. Both obstructive and restrictive lung disease have been reported in patients with SCA [49] and it is possible that there are physiological advantages for overnight oxygen or APAP, e.g. in improving daytime oxygen saturation [37] through improving gas exchange by overcoming upper or lower airway obstruction or increasing lung volume.

In addition to requiring additional safety data and exploring the physiological effects of overnight respiratory support, further work is needed to determine whether one of these alternatives is preferable to patients in terms of the inconvenience when compared with any possible benefits. To attempt to improve completion of diary data, the feasibility and acceptability of daily data collection on presence, site and severity of pain using a visual analogue scale for highest, pain and lowest daily pain using smartphone technology on an iPad mini (Apple Inc., Cupertino, CA, USA) also requires assessment.

The National Institute of Health Research (NIHR) Research for Participant Benefit (RfPB) stream has funded our group to undertake a Phase 2 randomised 2**-**arm trial of overnight respiratory support or standard treatment. As there are very few pilot data involving treatment for sleep**-**disordered breathing in this condition, it is important to assess the acceptability of overnight oxygen supplementation compared with APAP in participants before deciding on which form of overnight respiratory support to use as the treatment arm in the Phase 2 trial. In the participants and public involvement (PPI) work for the RfPB submission, no participant preference came out between the proposed two interventions to help make a decision on which intervention to choose, but these participants did not have first**-**hand experience of using either device. This pilot phase is designed to examine patient preferences after 1 week of using each device in randomised order and will also determine whether there is evidence that either form of overnight respiratory support has a short**-**term beneficial or detrimental effect on haematological variables or lung function.

There are 4 objectives for this study: (1) to assess whether overnight oxygen therapy or APAP is more acceptable to participants, (2) to assess whether there are any physiological or clinical benefits or risks of overnight oxygen therapy or APAP, (3) to assess the feasibility of using smartphone technology to collect daily information on site and severity of pain and (4) to identify the main cost drivers and potential cost implications of providing the intervention.

## Methods/Design

The study was given approval by NRES Committee East of England – Cambridge South (14/EE/0163) on 3 June 2014. Local ethical permission was granted by Guy’s and St Thomas’ hospital NHS Foundation Trust. This is a pilot cross**-**over interventional trial. Participants will have 2 interventions, overnight oxygen and APAP, for a week each in randomised order (weeks 2 and 4). There will be a week of baseline data collection (week 1), and a week of washout between the interventions (week 3).

Randomisation will be done by simple randomisation by an independent statistician at the University of Southampton. It will not be possible to blind the participant, study co**-**ordinator, sleep physiologist or psychologist to the order of treatment. However, the principal investigator, statistician and technician performing spirometry, i.e. those responsible for documenting the quantitative endpoints, will be blinded to which intervention is given in which order.

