### Participants

This pilot study will involve 20 participants, recruited regardless of symptoms of sleep**-**disordered breathing, which includes 10 children (age between 8 and 18 years) and 10 adults (age over 18 and above). All participants will be enrolled into the study for 29 days (i.e. 4 weeks).

Consenting participants with HbSS who are aged > 8 years and attend at Guy’s and St Thomas’ NHS Foundation Trust are eligible for this study. Participants will be excluded if they already have overnight respiratory support, if they have existing respiratory or decompensated cardiac failure or if they have any contra**-**indications to APAP therapy. Both inclusion and exclusion criteria are listed in Table 2.

**Table 2 Tab2:** Participant eligibility criteria for participation in the POMS2a trial

Inclusion criteria	
1	Recruitment will be through sickle cell clinics at Guy’s and St Thomas’ (including Evelina Children’s Hospital)
2	Age > 8 years
3	Informed consent with assent in accordance with the institutional policies (UK ethical committee) and European or US Federal guidelines must be signed by the participant or participant's parent or legally authorised guardian acknowledging written consent to join the study. Where appropriate, participants < 16 years will be requested to give their assent to join the study
4	HbSS diagnosed by standard techniques (HPLC, IEF and MS). Participating institutions must submit documentation of the diagnostic haemoglobin analysis
5	Able to speak and understand English
6	Participant or parent/guardian able to use iPad mini via wireless
Exclusion criteria	
1	Participant already on overnight respiratory support, or has used it in the past
2	Hospital admission for acute sickle complication within the past 1 month
3	Participant with > 6 admissions for acute sickle complications within the past 12 months
4	Existing respiratory failure
5	Decompensated cardiac failure
6	History of severe epistaxis
7	Trans-sphenoidal surgery, or trauma that could have left a cranio-nasopharyngeal fistula
8	Perforated ear drum
9	Bullous lung disease
10	Bypassed upper airway
11	Pneumothorax
12	Participant at increased risk of aspiration

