**Fig. 1 Fig1:**
[figure not shown]
Flow chart for the interventions and support from the respiratory physiologist

On day 1, the patient will attend the Day Care Unit at the hospital and data including baseline blood tests, PEDS**-**QL quality of life [50], daytime oximetry, will be collected. Adults will undergo lung function (spirometry and lung volume). The participant will be issued with an iPad mini with a validated smartphone app [38] for rating pain and symptom assessment and will be asked to complete daily data collection using this device for the duration of the whole study, taking approximately 5 minutes per day. They will be given an overnight oximeter to take home and will be asked to use this for 2 nights over the next week. The randomization codes will be provided at the start of the study by an independent statistician from the University of Southampton, who will use simple randomization to generate the order.

On day 8, the participant will have the first intervention (intervention 1), either oxygen or APAP, which will be delivered to their home and set up by the respiratory physiologist, or if they prefer, they can take the treatment home after explanation by the respiratory physiologist. They will be asked to use this for 7 nights and will have planned support calls (Fig. 1). The overnight oximeter will be collected by the respiratory physiologist and the data analysed. On day 15 the participant will return to the hospital Day Care Unit for medical assessment, blood tests, PEDS**-**QL quality of life assessment, daytime oximetry and the first qualitative assessment with lung function studies for the adults. Days 16**–**21 will be a washout phase with no intervention given, but ongoing daily data collection via the smartphone app on the iPad mini. On day 22 the participant will have the other intervention (intervention 2) installed at home and they will be asked to use this for the next 7 nights. On day 29, the participant will go to the Day Care Unit at the hospital for medical assessment, blood tests, PEDS**-**QL quality of life assessment, daytime oximetry and lung function tests (adults) and the second qualitative assessment. Adverse events and serious adverse events will be reported to the sponsor (Tables 4 and 5).

**Table 4 Tab4:** Laboratory findings to be reported to the sponsor within a maximum of 7 days

Variables	Measurement level that may be consider as adverse events
Haemoglobin	Fall of > 20 g/l from baseline is significant

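### Simple randomisation of device order in 20 people will usually give unequal orders; blocking within age group would be a cheap improvement for a one-off pilot that picks a device

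*Protocol article*

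**What the plan says.** The Methods/Design section of the protocol article fixes the method: "Randomisation will be done by simple randomisation by an independent statistician at the University of Southampton". The Procedure section repeats it, referring to a statistician "who will use simple randomization to generate the order", and the abstract agrees. Each participant has both devices "for a week each in randomised order (weeks 2 and 4", with "a week of washout between the interventions (week 3".

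Under Participants: "This pilot study will involve 20 participants", "which includes 10 children (age between 8 and 18 years) and 10 adults (age over 18 and above". No allocation ratio, block or stratification factor is named.

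Four other statements bear on how much order matters:

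- **Decision rule (Statistical analysis).** The Phase 2 device is chosen first on preference, then on apparent physiological benefit, then on cost.
- **Qualitative chart (Primary outcome).** Participants are to be arranged by device and by patient-or-carer status. Order is not among the groupings.
- **Quantitative comparison (abstract, Table 3).** Each arm is compared with baseline. Laboratory, quality-of-life and lung function measurements fall on day 1, day 15 and day 29, with no new baseline on day 22 before the second device.
- **Reporting (Statistical analysis).** Analyses are exploratory and mainly descriptive. A baseline table will compare the two order groups.

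**The concern.** In a two-period crossover, anything that changes between the first and second period cancels from a crude device comparison only to the extent that the two orders are equally frequent. With independent coin tosses for 20 people, and 10 in each age group, equal orders are unlikely.

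Two features make this design sensitive to order. First, people who have used respiratory support before are excluded, so nobody can compare the two devices from experience until the second has been used. The comparison is made around day 29, just after one device and about two weeks after the other. Secondly, both devices are compared with the same day-1 value, one at 14 days and the other at 28 days. Any drift or practice effect then falls on whichever device came second.

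At stake is whether part of an order effect is read as a difference between devices when the Phase 2 device is chosen. An analysis plan that is not shown might adjust for period, but it could not restore balance once allocation has been made.

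**Working it through.** The plan gives no figure for order balance, power or sample size, so there is nothing to reproduce.

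**Inputs.** n = 20, as two groups of 10 (Participants). Simple randomisation (Methods/Design). Assumed, because not stated: probability 0.5 for each order, independent between participants.

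**Step 1: chance of unequal orders.** The number starting with oxygen is Binomial(n, 0.5).

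- Whole trial: P(10:10) = C(20,10)/2^20 = 184,756/1,048,576 = 17.6%, so P(unequal) = 82.4%.
- Whole trial, tails: 12:8 or worse 50.3%; 13:7 or worse 26.3%; 14:6 or worse 11.5%.
- One group of 10: P(5:5) = 252/1,024 = 24.6%. P(7:3 or worse) = 2 × (120 + 45 + 10 + 1)/1,024 = 34.4%. This is the figure for the adults-only lung volumes.
- Both groups 5:5: 0.246² = 6.1%.
- At least one group 7:3 or worse: 1 − (1 − 0.344)² = 56.9%.

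**Step 2: effect on a crude device contrast.** Let δ be the true device difference and π the change from first to second period. The within-person difference has mean δ + π in one order and δ − π in the other. With a of n people in the first of these orders, the crude mean is δ + π(2a − n)/n.

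| Split | Share of π absorbed | Efficiency of period-adjusted contrast, 4a(n − a)/n² |
|---|---|---|
| 10:10 | 0% | 100% |
| 12:8 | 4/20 = 20% | 4 × 12 × 8/400 = 96% |
| 14:6 | 8/20 = 40% | 4 × 14 × 6/400 = 84% |
| 7:3 (n = 10) | 4/10 = 40% | 4 × 7 × 3/100 = 84% |

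Averaged over the binomial distribution, the absolute share absorbed is 17.6% for n = 20 and 24.6% for n = 10. Average efficiency after adjustment is 95% and 90% respectively.

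**Step 3: illustration for preference.** Assume no true preference, and that each person favours the device used last with probability between 0.60 and 0.75 (an assumed range).

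- At 12:8, the expected count for the device more often used last runs from 12 × 0.60 + 8 × 0.40 = 10.4 to 12 × 0.75 + 8 × 0.25 = 11.
- At 14:6, it runs from 14 × 0.60 + 6 × 0.40 = 10.8 to 14 × 0.75 + 6 × 0.25 = 12.
- The sampling SD of the count is √(20 × 0.60 × 0.40) = 2.2 to √(20 × 0.75 × 0.25) = 1.9, so about 2.

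**The case against.** The defence of the plan is substantial. Simple randomisation favours neither device in expectation. Every participant uses both, and a period-adjusted contrast is unbiased at any split in which both orders occur. Most overall splits are mild, and even at 14:6 the assumed recency effect moves the preference count by no more than about one sampling SD. The first device is discussed at its own interview, before the second is used, so the evidence is not a single question at the end. The baseline table by order would make an imbalance visible, and the analysis is exploratory. All of this stands, and it limits the point to an avoidable weakness.

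A reader might go further and infer that equal orders are indispensable, or that the device comparison is fair only if they are achieved. The documents do not support this. They mention no recency, learning or period effect and give no size for one, and adjustment is cheap at moderate imbalance.

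A reader might also infer that balance is needed within each age group for its own sake. Apart from the adults-only lung volumes, the article states no device contrast within an age group, so the 57% figure describes how uneven a group is likely to be and does not show harm to a planned comparison.

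Finally, "The randomization codes will be provided at the start of the study by an independent statistician" might be read, with an unblinded co-ordinator, as a failure of concealment. The article does not say who receives the codes, and not being blind to the order in use is different from seeing future allocations. Release mechanics are also detail that an article commonly leaves to the full protocol.

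What the defence does not answer is that being unbiased on average is a property over repeated trials. This one is run once, and its realised split enters a device decision in which order is not a named grouping.

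**Conclusion.** The point holds as a recommendation for a cheap design improvement. Under a 1:1 ratio, unequal orders are expected in 82% of such trials, and a marked split of 7:3 or worse in at least one age group in 57%. A severe overall split of 14:6 or worse is uncommon, at 11.5%.

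The consequence is conditional. If period or recency effects exist, a crude contrast takes in on average 17.6% of them in either direction, and 40% at 14:6. Adjusting for period removes this for the quantitative outcomes at a small to moderate loss of efficiency. Preference drawn from interviews has no equally simple adjustment, which is why balance at allocation and a display by sequence are worth having. The result rests on independent 1:1 allocation, on all 20 people completing both periods, and on order effects whose size is unknown.

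**What to change.** For the allocations still to be made (the Trial status section says recruitment continues), the same independent statistician should generate the order in permuted blocks of randomly varying size, separately for children and adults. Each participant must belong to exactly one age stratum. The present wording, "10 children (age between 8 and 18 years) and 10 adults (age over 18 and above", leaves an 18-year-old's group unclear, which matters only once age becomes a stratification factor.

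In the qualitative analysis, chart preference by sequence alongside the two groupings already planned. This is useful even if every allocation has already been made.

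The cost is a new list and a short amendment, with slight predictability at the ends of blocks. Imbalance already accrued cannot be undone, the gain depends on how many allocations remain, and withdrawals, replacements or incomplete blocks may leave small imbalances.
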